### Recruitment

We will recruit participants to the study on a rolling basis via advertisements from the Contemplative Studies Centre using the following streams: trial website, relevant university websites (eg, “volunteer for research” pages), media releases (and media), online advertisements, social media, newsletters, and email lists. We will also promote “snowballing” by sending a flyer through our research, education, practice, media, and advisory networks (and asking them to forward it to their networks) and further asking participants interested or participating in the study to share it on social media and refer a friend. If recruitment is slow, we will additionally consider paid online advertising (eg, through Google or Facebook).

Interested individuals will be directed to the trial website for information about the study, including a plain-language statement about the trial and a link to register interest in participating. The link will take interested individuals to a staged prescreener survey (hosted via Qualtrics) that assesses broad eligibility before looking at specific eligibility to understand the individual’s sociodemographic profile, meditation history, smartphone access and use, and mental health (refer to the Prescreening Measures section). The research team will confirm eligibility before individuals are invited via email to enroll in the study. To accept the invitation, participants will acknowledge that they have read the plain-language summary and will complete an online informed consent form informing them of the aims and particulars of the study and their right to withdraw from it at any time. Once enrolled, participants will receive a welcome email with a link to the first run-in task.

### Assignment of Interventions: Allocation and Blinding

After meeting the selection criteria and completing the run-in period and baseline measures, participants will be randomized to 1 of the 4 groups. Participants will be blinded to the dosing nature of the study and will only be told that they are participating in a trial to test the effects of a 28-day mindfulness meditation intervention. While participants will be informed of their group allocation (eg, group 1), they will not be informed of what the number refers to.

Randomization will be remote and computer based. The allocation process will be automatically concealed, so researchers will not be able to predict or influence who will be randomized to which group. Members of the research team will not be informed of participants’ allocation until after final analyses have been completed, and analyses will be conducted blind to group allocation.

Group allocation will be based on block randomization, with an equal number of participants allocated to each condition for every 24 participants. The randomization process consists of prepopulating a list of randomized allocated group orderings and putting this list in an Amazon Web Services Simple Queue Service First-In-First-Out queue (condition queue), from which group allocation occurs by polling an item from the queue. It is necessary to rebuild this condition queue regularly as queues have a maximum life span of 14 days. We decided to rebuild every night (as opposed to every 14 days), although the rebuilding process maintains the current allocated group orderings from the queue it replaces.

To generate the group ordering (condition list) that is placed on the condition queue, the following steps are taken using a Python script (Python Software Foundation) with the random seed set to 2023: (1) a list with 24 items constituting 1 block is created containing 6 occurrences for each group (ie, 1, 2, 3, 4, 1, 2, 3, 4...1, 2, 3, 4), (2) we randomize this list and then add it to the condition list, (3) this process is repeated 72 times to create a condition list of length 1728 (ie, 72 blocks of 24), and (4) this condition list is uploaded to the condition queue.

This method equates to block randomization as, for every 24 assignments to the condition list, an equal number of participants (ie, 6) will be randomly assigned to each group.

Participants flagged as suspicious and who fail to verify information used to determine their eligibility for the study within the designated time frame (ie, 1 week) will be removed from the study. If removal occurs after randomization, the group to which that participant was allocated will be added to a reassignment queue.

The group assignment for new participants will be based on the next allocation in the reassignment queue. If the reassignment queue is empty, allocation will revert to the condition queue.

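### The published recipe lets the allocation list be rebuilt up to a few possible shuffle calls, and refilled slots carry no random element, so the concealment claim is too strong

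*Protocol article*

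**What the plan says.** Everything on the mechanism stands in the protocol article under Assignment of Interventions: Allocation and Blinding.

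- **Claim.** Allocation is automatically concealed, so "researchers will not be able to predict or influence who will be randomized to which group".
- **Recipe.** The list is produced "using a Python script (Python Software Foundation) with the random seed set to 2023". For each block, "a list with 24 items constituting 1 block is created containing 6 occurrences for each group", in the starting order "ie, 1, 2, 3, 4, 1, 2, 3, 4...1, 2, 3, 4". Each block is shuffled and appended, and "this process is repeated 72 times to create a condition list of length 1728 (ie, 72 blocks of 24".
- **Delivery.** Allocations are drawn from a first-in-first-out queue. It is rebuilt nightly, but "the rebuilding process maintains the current allocated group orderings from the queue it replaces".
- **Refill.** When a participant is removed after randomization for failing verification, that participant's group enters a reassignment queue. Then: "The group assignment for new participants will be based on the next allocation in the reassignment queue". The condition queue is used only when the reassignment queue is empty.

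Eligibility Criteria says that checks continue throughout the study, that removal may follow randomization, and that the flagging method is preregistered but embargoed until data collection closes.

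**The concern.** Concealment means that nobody who can affect who enters or stays in the trial knows the next assignment. Automating the draw does not achieve this if the list behind it can be rebuilt. A seeded generator is deterministic, and nearly all of its inputs are printed here. Even apart from publication, whoever wrote the script could regenerate the list, and the article does not say that this person is separate from enrolment and verification.

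The refill rule is a second gap, and keeping the seed secret would not close it. It copies the removed participant's arm to a later entrant.

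What is at stake is selection through discretionary decisions. In this trial those decisions are less about recruiting than about whom to flag as suspicious, whom to ask for verification and whom to remove. Such decisions are not rare in principle: Results records that recruitment was paused because of fraudulent participants.

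**Working it through.** **1. Reproduce the stated list.** 72 blocks × 24 entries = 1728, as stated. 24 / 4 groups = 6 per group per block, as stated. Each group appears 72 × 6 = 432 times.

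**2. Can the list be regenerated?** Printed inputs: language (Python), seed (2023), starting order (1, 2, 3, 4 repeated), block (24), number of blocks (72), and a queue that keeps its order. Not printed: the shuffle function, and whether each block starts fresh or from the previous shuffled block. The recipe was coded in eight common forms (standard-library shuffle and sample; NumPy legacy shuffle and permutation; the newer NumPy generator; fresh or in-place blocks).

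| Check | Result |
|---|---|
| Same list on rerun | all 8 forms |
| Entries, and entries per group | 1728 and 432 in every form |
| Distinct lists among the 8 forms | 7 |
| Consecutive known allocations needed to tell the 7 apart, starting after entry 24, 70 or 200 | 3 in each case |
| The same, starting from the first entry | 27, because some forms share block 1 |

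The unnamed function therefore leaves a handful of candidates, and a short run of known allocations singles one out. These eight are the forms tried. They are not proof that the trial's script is among them.

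**3. How predictable is the next allocation from the condition list?**

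| Knowledge | Correct guesses |
|---|---|
| None | 1/4 = 25% |
| Seed secret, block known to be 24, all earlier allocations known (40,000 simulated blocks, guessing the group with most places left) | about 39%; about 1.3 of each 24 assignments are certain |
| Correct list and current queue position | 100% |

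**4. Refilled slots.** Suppose the reassignment queue is empty and a participant in group g is removed. The queue then holds g alone and is used before the condition queue, so the next entrant gets g with probability 1. If other slots are already waiting, the next entrant may get a different group, but no random element is described in that case either. The prediction requires knowing g. Possible sources are the regenerated list, the participant's own group number (participants are told it), or the weekly items on minutes per session.

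**5. What would dropping the refill cost in balance?** The number of removals after randomization is not given, so assume 2% to 10% of the 860 to be randomized, spread over arms at random. With R removals, the SD of the number falling in one arm is √(R × 1/4 × 3/4).

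- R = 0.02 × 860 = 17.2: √3.225 = 1.8
- R = 0.10 × 860 = 86: √16.125 = 4.0

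Against 860 / 4 = 215 per arm, this is negligible.

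**The case against.** The best defence is that predicting a list is not the same as steering people into arms. Eligibility is confirmed before enrolment, a 7-day run-in follows, and the draw is made automatically after the participant completes the baseline survey. The participant's own timing therefore sets the place in the queue. Someone exploiting the list would need the right shuffle call, the queue position, any pending refills and the number-to-dose key, which is not printed. The team is not to be told allocations until final analyses are complete. Removal follows a preregistered procedure and a 1-week limit. This largely stands, and it is why the likely bias is small. It does not rescue the sentence that allocation cannot be predicted, and it does not cover removal decisions: the flagging procedure is embargoed, so a reader cannot judge how much discretion remains.

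A reader might infer more than the documents support:

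- *Any reader can predict every assignment.* Not shown. An outsider lacks the shuffle call, the queue position and a run of known allocations.
- *The next entrant always receives the removed participant's arm.* This is so only if the reassignment queue was empty.
- *Those deciding removals see practice minutes.* Nothing says so, and the first weekly survey comes 7 days after baseline. It is a possibility to close off.
- *Refilling is unnecessary because the list has about twice the entries needed.* List length concerns supply and says nothing about balance after removals.
- *Refilling ties arm to calendar time and biases the comparison.* That needs removals that differ by arm, which nothing suggests. Under 5% of the sample had been recruited at the 2024 pause.
- *The seed was published while recruitment was open.* The publication date is not in the document. The future-tense text, the screening change dated March 12, 2025 and the possible 6-month extension make it plausible, not established.

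**Conclusion.** The concern holds in a limited form. The statement that allocation cannot be predicted or influenced does not hold for anyone who has the script and queue position, nor, for a refilled slot when the reassignment queue was empty, for anyone who knows the removed participant's arm. In those circumstances predictability is 100% rather than 25%.

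The documents do not allow the resulting bias to be sized. Automated assignment after baseline makes it probably small. The realistic route is verification and removal by people who could know the current or next allocation. This assumes that the trial's shuffle is an ordinary one and that the person holding the script is not separated from verification, a point on which the article is silent. Sample size and analysis model are unaffected. A correction is still worthwhile because it is cheap and lost concealment cannot be restored afterwards.

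**What to change.** **If allocations remain:**

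1. Generate the remaining list from a new, undisclosed seed held by someone independent of enrolment and verification, and record the date of the switch.
2. After a removal, give the next entrant the next condition-list entry, and retire the reassignment queue.
3. Keep those who decide on flagging and removal blind to arm and to reported practice minutes.
4. Release the seed only after recruitment closes. The protocol already applies this reasoning to its fraud-detection method.

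Varying the block size is optional; a block of 24 over four arms is already large.

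**If recruitment has closed:** qualify the concealment statement, report removals and refills by arm and date, and add a sensitivity analysis of the primary outcome excluding participants who entered through refilled slots.

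**Cost:** a little programming and a short amendment, with the ethics approval and registry and repository updates set out under Protocol Amendments. The imbalance between arms is trivial: an SD of about 2 to 4 removals per arm, against 215, under the removal rates assumed above.

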**Exclusion criteria**
Self-reported current or lifetime serious mental illness (eg, neurodevelopmental, schizophrenia spectrum, bipolar, obsessive-compulsive, trauma-related, dissociative, or personality disorder)Anxious and depressive symptoms in the severe range (defined by a score of >27 on the PROMIS Anxiety Short Form or >32 on the PROMIS Depression Short Form)Psychological distress symptoms in the severe range (Kessler Psychological Distress Scale ≥30)Threshold scores on prescreening and follow-up measures exceeded for mania, suicidal ideation, psychosis, repetitive thoughts and behaviors, and dissociationModerate or higher alcohol, tobacco, or drug useSelf-reported diagnosis of a neurological condition (eg, traumatic brain injury, amnesia, epilepsy, or stroke)Self-reported presence of any serious medical condition (eg, cancer, thyroid disorder, or multiple sclerosis)Recent bereavement or major lossHistory of unexplored, untreated traumatic experiences or adverse childhood events

The selection criteria will be self-assessed. Throughout the study, we will conduct various checks to verify the accuracy of the information provided in the prescreening survey to determine study eligibility. Participants whom we suspect provided inaccurate information may be required to verify specific details. If we cannot verify such information within 1 week, that participant will be deemed to have responded inaccurately and excluded from the study. Although we will make every effort to flag and remove inauthentic participants before randomization (ie, during the run-in period), in some cases, it may not be possible and, therefore, removal will take place after randomization. The Assignment of Interventions: Allocation and Blinding section provides details on how we will handle postrandomization exclusion.

Details on the procedure that we will use to flag and remove inauthentic participants were preregistered but are being kept confidential from study participants to avoid influencing behavior or actions that could compromise the procedure. Accordingly, the exact methodology has been embargoed [22] and will only be disclosed after data collection closes.

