### Statistical Methods

#### General Principles

The primary analysis will be undertaken on the primary outcome following the intention-to-treat approach [56]. The intention-to-treat analysis sample will consist of all randomized participants, assigning them to the arms they were randomized to independently of their subsequent behavior. An intention-to-treat approach was chosen for the primary analysis because the study’s main purpose is to test whether larger *prescribed* doses of mindfulness practice yield larger effects on well-being. Intention-to-treat analyses will also be conducted for all secondary outcomes. Additional secondary analyses will be conducted following the per-protocol approach for all outcome measures (ie, primary and secondary). For data collected at weekly increments between T0 and T1, measurement occasions will be nested within individual participants.

The comparisons of interest will be each intervention (10, 20, and 30 min) compared to one another and with the minimal dose for each outcome (mean difference and 95% CI).

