This study is being conducted entirely online. This has the advantage of allowing participants to practice in their homes and other familiar ecologically valid settings, although it also has the limitation of researchers having little control over the research environment. However, a common problem with internet-based interventions is high dropout rates and low adherence. Our primary analysis is to test the effectiveness of different doses, and therefore, our data will be analyzed on an intention-to-treat basis. As such, we are most concerned with the problem of high dropout rates. To minimize dropouts, we are offering financial inducements for participants to continue honestly reporting their practice amount and responding to questionnaires regardless of whether they are still completing the intervention. However, it is still in our interest to have high rates of adherence given that we will also analyze data on a per-protocol basis (ie, as secondary analyses only). To this end, we are using a run-in period to identify and exclude participants who are most likely to drop out and not complete the intervention before randomization. Given this use of the run-in period, we cannot make inferences about the likely adherence to similar mindfulness interventions in real-world settings. Therefore, while the use of a run-in period strengthens internal consistency, it introduces a selection bias. We will attempt to quantify this by reporting sociodemographic data and measures of mental health and well-being for people that complete the run-in period and compare them against those of people who do not. Despite the use of a run-in period, we still anticipate that adherence rates are likely to vary across dosage groups, with lower adherence at higher doses. This may limit our capacity to make inferences about the efficacy of different doses for the per-protocol analyses.

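### Flagged participants who are not verified within 1 week are removed and replaced after randomization, which the intention-to-treat definition does not allow for, and the plan never says how they are analysed

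*Protocol article*

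**What the plan says.** Three parts of the protocol article bear on this.

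- **Analysis set** (Statistical Methods, General Principles): "The intention-to-treat analysis sample will consist of all randomized participants, assigning them to the arms they were randomized to independently of their subsequent behavior". No exception is made.
- **Removal** (Eligibility Criteria, text after the exclusion list): checks on the prescreening answers run throughout the study. The plan concedes that "in some cases, it may not be possible and, therefore, removal will take place after randomization". The rule for an unresolved query is: "If we cannot verify such information within 1 week, that participant will be deemed to have responded inaccurately and excluded from the study".
- **Replacement** (Assignment of Interventions: Allocation and Blinding): removal applies to "Participants flagged as suspicious and who fail to verify information used to determine their eligibility for the study within the designated time frame". Then: "If removal occurs after randomization, the group to which that participant was allocated will be added to a reassignment queue". New entrants take the next allocation in that queue before the block list is used again.

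The eligibility text sends the reader to the allocation section for the handling of exclusions after randomization. That section deals only with re-allocating the place and says nothing about the analysis.

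**The concern.** The primary analysis set is defined in one place and altered in another. A person can be randomized, then flagged, then fail to answer within 1 week, and so be "that participant will be deemed to have responded inaccurately and excluded from the study" without anyone having shown that they were ineligible. Whether someone answers a request after allocation is a post-randomization event, and such events are what the intention-to-treat definition says must not decide who is analysed.

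Two things are at stake. First, two analysts could follow this text and build different primary sets. Second, removal from the study may mean that a T1 survey is never requested, and that loss cannot be repaired at analysis. The issue is live: the Results section reports that recruitment was paused because a significant number of entrants were fraudulent and ineligible.

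**Working it through.** **1. The two readings.**

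| Reading | Consequence |
|---|---|
| Removed participants leave the analysis | The definition in General Principles is wrong as written |
| Removed participants stay in the analysis | The eligibility and allocation sections must say so, and must say that their T1 survey is still requested |

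The text says removed from the study and never states outright that the data leave the analysis. Neither reading can be ruled out.

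**2. The plan's own figures.** Inputs from Sample Size: difference 1.97, SD 9.84, within-person correlation 0.83, two-sided alpha 0.02, power 80%, retention 80%.

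- Change-score variance: 9.84² × 2 × (1 − 0.83) = 96.83 × 0.34 = 32.92.
- Per arm: 2 × 32.92 × (2.326 + 0.842)² / 1.97² = 170.3, rounded up to 171. The plan states 172, or 688 in total.
- Number to randomize: 688 / 0.80 = 860, as stated.

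These figures stand if all randomized participants are analysed. What is open is the count. If m people are removed and replaced, 860 + m have been randomized. The plan does not say whether the 860 includes the m.

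**3. Whose removal can move the primary contrast.** The primary model (Effectiveness Analyses) uses T0 and T1 only, with a common baseline mean and unstructured covariance. Its estimate of the T1 mean in arm j is

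mean(Y1 in j) + β × [μ0 − mean(Y0 in j)],

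where both arm means are over people with a T1 score, β is the slope of T1 on T0, and μ0 is the common baseline mean. In the difference between two arms μ0 cancels. A participant with only a baseline score therefore adds essentially nothing to the contrast, whether kept or removed. A simulation with the covariance treated as known agreed: the two contrasts differed by about 1e-16. The secondary-outcome models also use T0.5, so this cancellation should not be assumed for them.

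Removal therefore matters for the primary contrast only among people who would have given a T1 score. That group is possible: Participant Compensation says surveys are offered and paid whether or not the person practises.

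**4. What the bias depends on.** Let q be the fraction of an arm's would-be T1 responders who are removed, and D the difference of their baseline-adjusted T1 mean from the full arm mean. Removal shifts the arm mean by −qD/(1 − q). The bias in a contrast is the difference of the two arms' shifts.

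- Equal q and equal D in both arms: bias 0.
- Assumed for illustration, q = 10% in one arm and 5% in the other, D = −2 in both: 0.222 − 0.105 = 0.12 points.
- Same q, D = −8: 0.889 − 0.421 = 0.47 points.

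Against the 1.97-point target these are 6% and 24%. If D is positive, or the larger q belongs to the other arm, the sign reverses. None of these q or D values comes from the documents, so they show how the formula behaves and do not estimate this trial's bias.

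**The case against.** The case on the other side has real force.

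- Removal needs a flag and then a failure to verify, so ordinary dropouts stay in the set.
- What is verified is information given before randomization, and the main check is placed in the run-in.
- The team is blind to allocation until after the final analyses.
- Excluding inauthentic entrants is defensible.
- The pause for fraud came with under 5% of the sample recruited, and extra screening followed. It says nothing about how often genuine participants would be removed.
- Attrition is to be described by arm.

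All of this stands, and it narrows the point. It does not settle which set is analysed. Blinding protects the decision to flag, but it does not make the participant's reply independent of the assigned dose.

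A reader might infer three stronger things that the documents do not support.

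- **That higher-dose arms are favoured.** The plan says "we still anticipate that adherence rates are likely to vary across dosage groups, with lower adherence at higher doses", but that concerns practice, and adherence is not the same as answering a verification request. The flagging rule is embargoed, so no link between arm and removal is shown.
- **That silent dropouts who are removed produce a bias of a few tenths of a point.** People with no T1 score do not move the primary contrast by being kept or removed. Any bias from their silence is ordinary missing-data bias, which the fix here would not cure.
- **That the published seed ("using a Python script (Python Software Foundation) with the random seed set to 2023") weakens the masking of removals.** Linking the list to people would also need the code and the queue order. Knowing the list does not make anyone fail verification.

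**Conclusion.** The point holds as an unresolved conflict over who is in the primary analysis. The intention-to-treat definition covers all randomized participants regardless of later behaviour. The eligibility and allocation sections exclude and replace some of them for not being verified after allocation. The article does not say whether they are analysed or whether they count toward the 860.

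The effect on the primary contrast is of unknown size and direction. It is zero unless flagged genuine participants who fail verification, and who would have supplied T1 scores, differ between arms in number or in outcome. This rests on the stated T0/T1 model. The sample-size figures do not change. It should be settled before unblinding, and the T1 invitation must be settled while follow-up is still running.

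**What to change.** Reconcile General Principles with the eligibility and allocation sections, as follows:

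1. Exclude a randomized participant from the primary set only when ineligibility or inauthenticity is established from prerandomization information, by assessors blind to arm and outcome.
2. Keep every other flagged non-verifier in the arm they were randomized to, and continue to invite them to the T1 survey.
3. Report removals by arm and reason.
4. Rerun the primary model on all randomized participants as a sensitivity analysis.
5. State that replacements add to the analysis set and do not substitute for the people removed, and say whether those removed count toward the 860.

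Optionally, continue the existing block list in place of the reassignment queue. It has 72 × 24 = 1,728 places, which leaves 1,728 − 860 = 868 spare.

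The cost is protocol wording and one further model run, plus a small script change if the queue is dropped. The downside is that some unverified records stay in the primary analysis, and arm sizes may be slightly unequal.
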